**Objectives:**

To describe the research design for an exploratory trial examining the acceptability, hypothesised process of change and implementation of a social norm marketing campaign designed to correct misperceptions of normative alcohol use and reduce levels of misuse, implemented alongside a university wide alcohol harm reduction toolkit. It also assesses the feasibility of a potential large scale effectiveness trial by providing key trial design parameters including randomisation, recruitment and retention, contamination, data collection methods, outcome measures and intracluster correlations.

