An exploratory cluster randomised design with nested process evaluation will be used to identify appropriate outcome measures and data collection methods, test randomisation processes, assess the extent of contamination across trial arms and establish recruitment and retention rates and intra-cluster correlations to help inform sample size for any future definitive trial. It will also identify whether the intervention effectively mobilises the underpinning theory and that this is sufficient to bring about hypothesised responses in terms of awareness, engagement and changed perception of norms. Whilst intervention acceptability and implementation processes will be assessed within the process evaluation.

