Universities in the study also receive a toolkit to promote institutional responsibility for prevention, audit current alcohol misuse policies and practices and which provided advice and guidance on prevention. The toolkit was developed by a National Union of Students (NUS) intervention project officer in consultation with the universities in the study. It was distributed to key university stakeholders in October 2011 with the intention of developing a supportive environment for the intervention. Control halls will be exposed to the toolkit only. The toolkit and social norms intervention were developed collaboratively by Drinkaware, NUS Wales and the Welsh Government following a review of previous interventions and support from an academic supervisor. Their implementation was facilitated by a dedicated NUS project officer. Given the nature of the intervention, it was not possible to blind participants to condition.

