Finally, within the survey described above, to assess intervention reach, students will be asked to indicate whether they had seen the intervention materials in their own hall of residence, or in another students' hall of residence. To assess recall, students who recalled seeing any of the norms materials will be asked to identify core messages from a list. Students will also be asked whether messages within the materials were credible and relevant, and whether they felt that exposure to the materials had influenced their normative perceptions or behaviour. These questions will be identical for students in control and intervention halls, allowing assessments of contamination between trial arms. The survey also includes a number of bespoke items from the intervention survey, which informed the social norm intervention, but only where these are linked to specific intervention communications (e.g. some materials focused on round buying behaviour and alternating alcoholic and soft drinks, hence items assessing the prevalence of these behaviours are retained).

Hall of residence managers will be asked for their consent for researchers to visit halls to monitor the placement of campaign materials. Prior to group interviews, an information sheet would be provided, with participants offered the opportunity to ask questions prior to obtaining informed consent. Since part of the process evaluation requires asking different questions of intervention and control premises representatives, the research team members who conduct the process evaluation will be unblinded.

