### Analysis

In order to assess exposure to intervention materials and contamination between trial arms, percentages of students within the intervention and control groups reporting having seen each of the intervention materials i) in their own hall of residence and ii) in another students' hall of residence will be examined. Among those students reporting exposure to intervention materials, percentages correctly identifying the messages within them will be calculated for each trial arm. Percentages of students reporting each level of agreement with statements regarding the credibility, relevance and perceived impacts of intervention materials will also be examined for each trial arm.

Whilst the study is likely not sufficiently powered to detect impacts on behaviour, it is likely that relatively large changes in perceived norms will be necessary to produce small changes in behaviour. Hence, regression analyses, with random terms to adjust for clustering at the hall level, and fixed terms to adjust for stratification variables, will examine differences between intervention and control participants in terms of normative perceptions for alcohol consumption and alcohol related consequences. Comparisons between trial arms will be conducted on an intention-to-treat basis. Secondary analyses would compare halls on the basis of researcher observations of whether or not materials were placed.

To inform the design of a potential large scale definitive trial with sufficient power to detect changes in behaviour, intra-cluster correlations and standard deviations will be calculated for total number of units per week. Response rates will be calculated in each trial arm. The percentage of students reporting willingness to provide hair samples will also be presented, whilst among those students reporting that they would only do so if paid, percentages reporting that each level of payment would be required would be presented.

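### Contamination, a stated deliverable, rests mainly on prompted self-report, and no decoy material or control-hall placement check is described that would separate real spillover from false recognition

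*Protocol article*

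**What the plan says.** The Abstract (Objectives) lists contamination among the "key trial design parameters including randomisation, recruitment and retention, contamination, data collection methods, outcome measures and intracluster correlations" that the trial is to supply. The Background repeats the aim to "assess the extent of contamination across trial arms and establish recruitment and retention rates". The Intervention section sets the contrast: "Control halls will be exposed to the toolkit only".

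The measurement is described under Process evaluation. In the follow-up survey, "students will be asked to indicate whether they had seen the intervention materials in their own hall of residence, or in another students' hall". Then "students who recalled seeing any of the norms materials will be asked to identify core messages from a list". The inference drawn is that "These questions will be identical for students in control and intervention halls, allowing assessments of contamination between trial arms".

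The Analysis section tabulates, by arm, the percentage who report seeing each material, split by own hall and another student's hall. It adds: "Among those students reporting exposure to intervention materials, percentages correctly identifying the messages within them will be calculated for each trial arm".

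Other information bears on the question:
- place of residence (Demographics);
- group interviews of up to 6 students in one hall per university without the campaign;
- a questionnaire to all wardens;
- researcher visits to check placement, listed for each intervention hall.

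**The concern.** A prompted question about having seen a poster or beer mat draws some positive answers from people who never saw it. In intervention halls these sit among many true sightings. In control halls, where true exposure is meant to be low, they may make up much of the reported figure.

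The planned checks do not resolve this:
- **Message identification** is asked only of students who already claim exposure. It is reported as a separate percentage and does not correct the exposure figure.
- **Shared messages.** Table 1 gives the October posters and beer mats the same messages, so recalling a message cannot confirm which of the two was seen.
- **Placement visits** are listed for intervention halls only, so a control-hall claim to have seen an item in the student's own hall has no described observational check.
- **Interviews** in one control hall per university can suggest explanations but cannot give a rate.
- **Location.** The two options leave nowhere to record sightings outside halls, although beer mats, leaflets and glasses are portable.

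The Discussion says that a definitive trial needs an understanding of contamination. Ten per cent real spillover and ten per cent false recognition would call for different responses, and the raw percentage cannot tell them apart.

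**Working it through.** **The plan's own figure.** The protocol states no contamination or false-recognition figure, so there is none to reproduce. Its only power statement (80% for 0.2 SD at 32 per hall and 0.23 SD at 20 per hall) does reproduce: a hall-level t-test on 48 degrees of freedom gives 80.5% and 81.2%. That has no bearing on this point.

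**Inputs.** All of the following are assumptions, because the protocol gives none of them:
- c, true exposure in control halls: 0% or 10%;
- f, the probability that an unexposed student says yes: 5% to 15%;
- s, the probability that an exposed student says yes: 60% or 100%.

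**Step 1. What is identified.** With r the true reach in intervention halls:
- reported control exposure = c·s + (1 − c)·f
- reported intervention exposure = r·s + (1 − r)·f

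The survey gives two percentages for four unknowns (c, r, s, f). Asking the same questions in both arms makes it plausible that s and f are common. The difference between arms is then (r − c)(s − f), but c itself is still not identified.

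**Step 2. Reported control exposure.**

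| c | s | f = 5% | f = 10% | f = 15% |
|---|---|---|---|---|
| 0% | any | 5% | 10% | 15% |
| 10% | 100% | 14.5% | 19% | 23.5% |
| 10% | 60% | 10.5% | 15% | 19.5% |

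For example, with c = 10%, s = 60% and f = 5%: 0.10 × 0.60 + 0.90 × 0.05 = 0.105.

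**Step 3. Direction.** The bias is (1 − c)·f − c·(1 − s). With c = 10% and s = 60% it is zero at f = 0.10 × 0.40 / 0.90 = 4.4%. Below that, contamination is understated. With c = 0 the bias is f and can only be upward.

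**Step 4. What a decoy adds.** Endorsement of a never-distributed item estimates f. Take 800 respondents per arm (25 halls of 32) and borrow the protocol's intra-cluster correlation of 0.03, which it assumed for alcohol units. The design effect is 1 + 31 × 0.03 = 1.93. At f = 10% the standard error is √(0.10 × 0.90 × 1.93 / 800) = 0.0147, a 95% margin of about ±2.9 percentage points. With 500 per arm (25 halls of 20) the design effect is 1.57, the standard error 0.0168 and the margin about ±3.3 points. Either is precise enough to be useful.

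**Step 5. Limits of correction.** Take (observed − f)/(1 − f) with f = 10%. If recall is complete, (0.19 − 0.10)/0.90 = 10%, the true value. If s = 60%, (0.15 − 0.10)/0.90 = 5.6%, below the true 10%. The correction holds only if recall is full and decoys attract the same f as real items.

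**The case against.** The strongest reply is that this asks for a refinement of an exploratory survey whose questionnaire is not shown. Much of that stands.

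- **A reader might infer that there is no decoy.** The article does not support that. It condenses a fuller protocol, and its reference to correct identification from a list suggests that wrong options may exist. The most that can be said is that none is described, and that the detailed analysis list mentions neither decoy endorsement nor a correction.
- **A reader might infer that contamination will be overstated.** Step 3 shows that this is not fixed. Under-recall offsets false recognition, and sightings outside halls that have no response category would be missed.
- **A reader might infer that the definitive trial will be mis-sized.** If a planner treated f as all-or-nothing dilution of a 0.1 SD effect, the sample would grow by 1/(1 − f)², that is 1.11, 1.23 and 1.38 times at f = 5%, 10% and 15%. But the protocol sets no such rule. The inputs it lists for planning that trial are intra-cluster correlations, standard deviations, response rates and willingness to give hair samples. The multipliers are hypothetical.
- **The setting may not favour confusion strongly.** The toolkit went to university stakeholders, and no student-facing toolkit messages are described. A second wave of materials came in January 2012, shortly before the survey of mid-February to the end of March.
- **Planned data give a rough gauge.** Own-hall claims in intervention halls where researchers saw no placement would hint at f. The consent wording for visits is also not limited to intervention halls, although nothing says that control halls will be visited.

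What does not fall is the identification problem. None of these sources gives f for control halls, and the stated measure remains the raw percentage.

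**Conclusion.** The concern holds as a limitation of measurement. The contamination estimate rests mainly on unvalidated, prompted self-report, and nothing described separates a true control-hall sighting from a false one. With no true contamination the reported figure equals f, so 5% to 15% under the assumed range. With 10% true exposure it runs from 10.5% to 23.5% across the assumed f and s. These sizes are illustrations, not estimates from the protocol. The sign of the net bias is unknown, and no consequence for the size of a definitive trial can be derived from the text. Reach in intervention halls is affected by the same two errors. No stated figure is wrong and no passages conflict. It is worth acting on because contamination is a named deliverable and the remedy is small: a cheap improvement.

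**What to change.** **In the survey, if not already present:**
- add one or two never-distributed, neutrally worded materials in the campaign's style to the exposure list;
- add some never-used messages to the recall list;
- place both after the norms measures, so that invented content does not affect answers on perceived norms;
- add an elsewhere option to the location question.

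**In the Analysis section:**
- report decoy endorsement by arm beside the raw exposure percentages;
- report having seen a material and correctly identified its message as a percentage of all respondents in each arm, not only of those claiming exposure;
- give (observed − f)/(1 − f) as a sensitivity figure, stating that it assumes the same f for decoys and real items and full recall;
- interpret contamination and reach from all of these together, with the interviews and placement observations, and do not let the corrected figure replace the raw one.

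Students who tick a decoy should not be reclassified as unexposed, since some will also have seen real materials.

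**Cost.** A few extra tick-boxes, a slightly longer survey and some extra lines of analysis. The correction is only approximate, and on the paper version question order cannot be enforced.

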### Analysis

In order to assess exposure to intervention materials and contamination between trial arms, percentages of students within the intervention and control groups reporting having seen each of the intervention materials i) in their own hall of residence and ii) in another students' hall of residence will be examined. Among those students reporting exposure to intervention materials, percentages correctly identifying the messages within them will be calculated for each trial arm. Percentages of students reporting each level of agreement with statements regarding the credibility, relevance and perceived impacts of intervention materials will also be examined for each trial arm.

Whilst the study is likely not sufficiently powered to detect impacts on behaviour, it is likely that relatively large changes in perceived norms will be necessary to produce small changes in behaviour. Hence, regression analyses, with random terms to adjust for clustering at the hall level, and fixed terms to adjust for stratification variables, will examine differences between intervention and control participants in terms of normative perceptions for alcohol consumption and alcohol related consequences. Comparisons between trial arms will be conducted on an intention-to-treat basis. Secondary analyses would compare halls on the basis of researcher observations of whether or not materials were placed.

To inform the design of a potential large scale definitive trial with sufficient power to detect changes in behaviour, intra-cluster correlations and standard deviations will be calculated for total number of units per week. Response rates will be calculated in each trial arm. The percentage of students reporting willingness to provide hair samples will also be presented, whilst among those students reporting that they would only do so if paid, percentages reporting that each level of payment would be required would be presented.

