## Background

Excessive alcohol consumption among university students has been linked to a range of adverse outcomes, including educational difficulties, psychosocial problems, antisocial behaviours, injuries, risky sexual behaviours and drink driving [1]. In the United Kingdom, alcohol consumption levels amongst university aged adults increased rapidly during the 1990s [2]. Recent studies suggest that just over half of UK university students 'binge drink' (i.e. consume 5 or more drinks in one sitting) at least once per week [3,4], whilst as many as 80% binge drink at least once a month [4]. One recent study estimated average alcohol consumption at 25 units per week for 1^st ^year male UK undergraduates and 16 for 1st year women [5], significantly above current public health recommendations. Recent UK government policy of increasing the percentage of young people going to university has perhaps had the effect of exposing a larger proportion of the population to this high-risk drinking environment.

Alcohol consumption amongst university students has to date proved highly resistant to intervention efforts [6]. One approach, which has shown some promise in experimental studies, is addressing the perceived social norms that are posited to influence alcohol consumption [7]. Perceived norms take the form of descriptive norms, with behaviour modelled through observation of the behaviour of significant others; or injunctive norms, where the individual perceives that their peers expect them to behave a certain way. Interventions underpinned by the social norms approach argue that normative perceptions are highly fallible, with students often overestimating real alcohol consumption patterns among peers [8]. Hence, through providing feedback and correcting misperceptions regarding the behaviours and social expectations of peers, alcohol drinking behaviours may be reduced. Social norms interventions have typically involved provision of mailed, web-based or face-to-face feedback on individual's drinking behaviour and how this compares to norms for their peer group, or social marketing campaigns to promote awareness of actual norms. A recent Cochrane review concluded that feedback-based interventions delivered via the internet or face-to-face on a one-to-one basis appeared to reduce student drinking behaviours, though mailed or group feedback were less effective, and findings for social marketing campaigns were equivocal [7].

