### The intervention

The intervention is a social norm marketing campaign, which aims to correct misperceptions regarding the behaviours and social expectations of peers and in so doing influence alcohol consumption. The campaign will be delivered in two phases between October 2011 and May 2012 in intervention halls of residence in four universities and will use a variety of materials encompassing posters, beer mats/coasters, leaflets, meal planners and drinking glasses. The campaign will be implemented by university accommodation staff. Social norm messages were based on the results of a survey of first year university students conducted in study universities in late April/May 2011 which identified discrepancies between norms and behaviours. Table 1 highlights the intervention materials and main social norm messages within them.

**Table 1 T1:** Social norms intervention components and examples of core messages communicated within them

Timing	Material	Core message
October 2011	Posters	'Those around you are drinking less than you think: students overestimate what others drink by 44%' 'Most of us significantly overestimate the amount that others drink'
	
	Beer mats/coasters	'Those around you are drinking less than you think: students overestimate what others drink by 44%' 'Most of us significantly overestimate the amount that others drink'
	
	Window stickers	'Few of us approve of people who drink to the point of losing it'

January 2012	Posters	'Most students drink to feel confident, but 70% have embarrassed themselves when drunk'
	
	Drinking glasses	'Time for a break? Many students limit their drinking by including soft drinks in the night'
	
	Gender specific leaflets	Males: '86% of Males have never damaged their halls of residence when drunk' Females: 'How much do you think the average female first year student drinks? Halve it. It really is less than you think.'

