### Randomisation

Blind remote randomisation was used to allocate halls of residence to receive the social norms plus toolkit intervention or toolkit only. Halls were stratified by institution and halls allocated alternately in a list ordered by size, with the group allocation determined by one random number within each stratum.

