#### Demographics

Measures of gender, age, ethnicity, international/home student status, course studied and place of residence will facilitate an examination of the representativeness of the sample, to assess comparability between groups of students assigned to receive/not receive the social norms intervention and assess potential contamination between trial arms.

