### Data collection

At four months after initial implementation of the intervention, measures will be collected via a survey to all 1^st ^year university students, offered in web and paper format. They will be recruited via nominated university distribution contacts, who will circulate the link to first year students via email and electronic notice boards between mid-February and the end of March 2012. At least one reminder will be emailed to students during the data collection period. On completion of the questionnaire, data will be captured and processed by a market research company, who will prepare a complete anonymised dataset for analysis. Heads of student services provided consent for the conduct of the survey and students will not be able to complete the survey without completing informed consent tick-boxes. Students will not be asked to provide any identifiable information, other than email addresses, which will be used purely for the purpose of selecting a winner for the £100 prize draw in each university, offered as an incentive for participation. Email addresses will be separated from responses to the web survey and destroyed after the prize draw.

In an attempt to boost student responses, residence hall managers will be asked to promote the survey and the prize draw to residents. To compare the efficacy of two data collection approaches, a paper copy of the questionnaire will be distributed to student halls of residence via accommodation managers, inviting students either to complete the paper copy and return it to the research team in a freepost envelope, or to go to the web-page to complete the survey online. Questionnaires completed in paper form will be returned to the research team in freepost envelopes. These will be stored in a locked cabinet until the web survey data-file is received from the survey company, at which point, questionnaires will be retrieved, data entered into the data-file, and questionnaires returned to the cabinet. Participants will be offered the opportunity to enter a prize draw, with £100 offered to one winner in each participating university by supplying a university email to be kept separately to questionnaire responses. Email addresses will be recorded on a detachable sheet at the start of the questionnaire, which will be separated from the questionnaire once received, with the email address entered into a separate spread sheet and the paper copy destroyed.

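### The between-arm regression adjusts only for hall clustering and the stratification variables; gender, collected and prognostic for units per week on the protocol's own figures, should be a pre-specified covariate

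*Protocol article*

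**What the plan says.** All references are to the Protocol article.

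- **Model (Analysis).** Arms are compared by "regression analyses, with random terms to adjust for clustering at the hall level, and fixed terms to adjust for stratification variables". The model is applied to "differences between intervention and control participants in terms of normative perceptions for alcohol consumption and alcohol related consequences". Units per week, the primary outcome, is not named in that sentence; for it the section plans an ICC and a standard deviation.
- **Allocation (Randomisation).** "Halls were stratified by institution and halls allocated alternately in a list ordered by size". The stratification variables are therefore institution and, at most, the size ordering.
- **Gender and consumption (Background).** A cited study put "average alcohol consumption at 25 units per week for 1^st ^year male UK undergraduates and 16 for 1st year women".
- **Use of gender (Demographics).** "Measures of gender, age, ethnicity, international/home student status, course studied and place of residence will facilitate an examination of the representativeness of the sample", and also a check of comparability between arms and of contamination. No use as a covariate is given.
- **How respondents arise (The intervention, Data collection, Sample size).** Students are not blinded. The survey is open to all first-year students about four months after the campaign starts, and "residence hall managers will be asked to promote the survey and the prize draw to residents". Response is assumed to be 40% or 25%. The May 2011 survey came before the 2011/12 campaign year and gives no baseline for the respondents.

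**The concern.** Randomising halls balances halls in expectation. It does not balance who chooses to answer months later, in an unblinded setting, when most students are expected not to answer. With no baseline drinking measure, a difference in the make-up of the responding groups enters the contrast directly. Gender is the one collected variable for which the document itself shows a large difference in consumption, and the campaign cannot change it.

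The document plans a comparability check but does not say what follows if the arms differ. That leaves the choice of covariate until after the data are seen. At stake is a shift in the arm contrast that is not negligible beside the effects below 0.1 SD that the Sample size section calls realistic, together with a small loss of precision.

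**Working it through.** **1. The plan's own figures.** Inputs from Sample size and the Abstract: 25 halls per arm, m = 32 or 20 respondents per hall, ICC 0.03, two-sided alpha 0.05.

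- Design effect = 1 + (m − 1) × 0.03 = 1.93 (m = 32) or 1.57 (m = 20).
- Effective n per arm = 25m / design effect = 414.5 or 318.5.
- Power with t on 48 df: 80.5% at 0.2 SD and 81.2% at 0.23 SD. The normal approximation gives 82.1% and 82.7%.

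The stated 80% is reproduced, so the point does not rest on a sample-size error.

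**2. Chance imbalance in male share among respondents.** Assumptions: half of respondents male, equal hall sizes, no selective response. SD of the arm difference = √[0.25 × (1 + (m − 1)ρ) × 2 / (25m)], where ρ is the ICC of gender by hall. The documents give no ρ.

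| m | ρ | SD | 95% range (points) | Shift at 9 units (units/week) |
|---|---|---|---|---|
| 32 | 0 | 0.025 | ±4.9 | ±0.44 |
| 20 | 0 | 0.032 | ±6.2 | ±0.56 |
| 32 | 0.10 | 0.051 | ±9.9 | ±0.89 |
| 20 | 0.10 | 0.054 | ±10.6 | ±0.95 |

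**3. Shift per unit of imbalance.** Gender gap = 25 − 16 = 9 units/week. A 5-point difference in male share gives 0.05 × 9 = 0.45 units. The documents give no SD for units per week, so it is assumed: 0.45/15 = 0.030 SD, 0.45/20 = 0.023 SD, 0.45/25 = 0.018 SD. At 10 points the shift is 0.9 units, or 0.060, 0.045 and 0.036 SD.

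**4. Precision gained by adjustment.** With half the students male, the share of variance explained is 0.25 × (9/SD)². The detectable difference is multiplied by √(1 − that share), with the outcome ICC held at 0.03. Unadjusted detectable differences (normal approximation, 80% power) are 0.195 SD at m = 32 and 0.222 SD at m = 20.

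| Assumed SD | Variance explained | Adjusted, m = 32 | Adjusted, m = 20 |
|---|---|---|---|
| 12 | 14% | 0.180 | 0.206 |
| 15 | 9% | 0.186 | 0.212 |
| 20 | 5% | 0.190 | 0.216 |
| 25 | 3% | 0.191 | 0.218 |

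The detectable difference falls by about 2-7% over this range. Steps 3 and 4 apply to units per week only.

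**The case against.** The strongest case against has several parts.

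- **The specification is standard.** Adjusting for stratification variables is correct, and a fuller covariate list is often left to an analysis plan. This has weight, but here the article itself states the adjustment set and gives gender other uses.
- **The evidence concerns a different outcome.** The 25 and 16 units are own consumption, while the regression sentence names perceived norms and consequences. This stands: no gender gap is given for those outcomes, so prognostic strength is shown for units per week only. Table 1 lists gender-specific leaflets, which suggests that the authors see norms as gender-related, but that is not a figure.
- **Chance imbalance has expectation zero and is already in the standard error.** True. Adjustment then improves precision rather than removing bias. Only differential response by gender would be systematic, and the documents give no figure for it.
- **The trial is exploratory** and says that it is likely underpowered for behaviour. This limits the consequence.

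A reader might also be tempted by two stronger claims that the documents do not support.

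- *That gender is unbalanced by design.* It is merely not a balancing factor. The one related step in Inclusion/exclusion criteria, leaving out the only female-only hall, was taken for the sake of balance.
- *That adjustment would cure self-selection.* A reader might note that the campaign is run on the hall side ("The campaign will be implemented by university accommodation staff") and that hall managers promote the survey; that these are the same people is an inference. Suppose the log-odds of response fell by an assumed 0.1 per SD of drinking in one arm only. The responder mean would shift by about 0.1 × (1 − 0.40) = 0.06 SD, or 0.1 × (1 − 0.25) = 0.075 SD. Gender adjustment would remove only about the 3-9% of this that gender explains (SD 15-25), that is 0.03 × 0.06 ≈ 0.002 to 0.09 × 0.075 ≈ 0.007 SD. That scenario is no argument for the covariate.

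**Conclusion.** The point holds as a modest improvement to the model. The stated adjustment set omits a collected variable that the campaign cannot affect, that is prognostic for the primary outcome on the protocol's own figures, and whose balance among respondents the design does not secure. Imbalances of around 5 points are within chance. They would move a units-per-week contrast by 0.02-0.03 SD, which is 18-30% of a 0.1 SD effect.

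This rests on an assumed SD of 15-25, an even gender mix and the cited 9-unit gap applying to these students. Imbalances near 10 points need an assumed gender ICC of about 0.10 or differential response. Nothing in the document shows that the arms do differ in gender, that gender predicts perceived norms or consequences, or that age or home/international status is prognostic. The importance is minor to moderate for an exploratory trial.

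**What to change.** In Analysis, state that gender enters as a fixed effect, alongside the stratification variables and the hall random effect, in the between-arm models for perceived norms and alcohol-related consequences and in any arm comparison of units per week. Report the strata-only model as a sensitivity analysis. Age and home/international status may be added as further pre-exposure covariates, provided that they are named in advance.

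The cost is one sentence of analysis wording, one extra model per outcome and a simple stated rule for the few records with missing gender. No new data are needed. The report should say that the adjustment addresses only imbalance carried by gender.
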